#### Secondary outcomes

Echocardiography (from baseline to weeks 4 and 12): Echocardiographic measurement of LVEF, SV, left ventricular end-diastolic diameter (LVEDD), left ventricular end-systolic diameter (LVESD), ratio of left ventricular early diastolic fast filling peak to late diastolic filling peak (E/a), and ratio of early diastolic velocity of mitral valve to early diastolic annular velocity (E/e).Hamilton Anxiety Scale, Hamilton Depression Scale (from baseline to weeks 4, 8, and 12). HAMA is mainly used to assess the severity of patients’ anxiety symptoms, generally more than 14 points considered meaningful. HAMD is one of the most commonly used scales to assess depression in clinical practice, and more than 20 points are considered meaningful.Rate of increase and decrease of anti-arrhythmia western medicine (from baseline to weeks 4, 8, and 12).SF-36 (from baseline to weeks 4, 8, and 12). The MOS Item Short from Health Survey (SF-36) was used to evaluate the quality of life of patients.NT-proBNP (from baseline to weeks 4 and12): NT-proBNP is a reliable and sensitive indicator of heart failure. One of the causes of heart failure is atrial fibrillation. Its elevation is positively correlated with the severity of heart failure. Changes in the levels of NT-proBNP in each group will be measured before and after treatment.Integral TCM syndrome score (from baseline to weeks 4 and 12; the scores and details are presented in Tables 1 and 2): A scale of 0–6 points and half quantitative points will be used to score the patients according to the severity of clinical symptoms [7].
° Significant effect: inhibition or complete suppression of primary and secondary clinical symptoms and reduction of syndrome score by ≥ 70%° Effective: significant improvement in clinical symptoms, and reduction of syndrome score by 30–70%° Ineffective: reduction of treatment syndrome score by < 30%° Aggravation: the score after treatment exceeds the score before treatment

**Table 1 Tab1:** Traditional Chinese Medicine symptom score

	None	Mild	Moderate	Severe
Palpitation	0	2	4	6
Panting	0	2	4	6
Lassitude	0	2	4	6
Expectoration	0	2	4	6
Weight	0	2	4	6
Tongue fur and type of pulse	0	2	4	6

**Table 2 Tab2:** Detailed description of symptoms according to Traditional Chinese Medicine

	None	Mild	Moderate	Severe
Palpitation	No symptom	Occasional occurrence; slight uncomfortable feeling	Regular occurrence; lasts for a long duration; intense uncomfortable feeling	Frequent occurrence; uncontrolled; Considerable influence on the quality of life
Panting	No symptom	Slight and no influence on routine activities	Heavy, but can still manage to perform routine activities	Too heavy, cannot perform routine activities
Lassitude	No symptom	Slight and can work	Heavy, but can still manage to work	Too heavy, cannot work or continue routine activities
Expectoration	No symptom	Less sputum	Moderate amounts of sputum	A lot of phlegm
Weight	BMI:18.5-24	BMI:24-27	BMI:27-30	BMI≥30
Tongue fur	Thin white tongue	Tongue coating is thin and yellow	Thin glossy coating of the tongue	Moss greasy thick

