### Diagnostic criteria

The diagnosis of atrial fibrillation can be confirmed based on clinical manifestations, physical examination, and electrocardiographic characteristics as follows [7]: (1) clinical manifestations: palpitation, chest tightness, and decreased exercise tolerance; (2) physical examination: heart auscultation varies in the heart rate, and heart sounds vary in strength, rhythm is absolutely irregular, and pulse is short; and (3) electrocardiogram: *P* wave disappear, the *f* wave replaces it, the frequency is about 350–600 times, and the QRS complex rhythm is absolutely irregular.

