### Inclusion criteria

The inclusion criteria are as follows: (1) The patient’s age is 18–85 years; (2) atrial fibrillation, seizure frequency ≥2 times a month (at least one ECG diagnosis); (3) the main syndrome of TCM syndrome differentiation was Qi deficiency-caused phlegm stagnation; and (4) have a correct understanding of the significance of the study, have good compliance with the observation and evaluation of the researcher, and voluntarily accept the clinical trial and fill in the clinical consent form.

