### Interventions

Eligible patients will be randomized to either the treatment group or the control group. The treatment group was treated with HTDJ plus western medicine. The control group was treated with placebo granules plus western medicine. Western medicine includes cardioversion drugs and heart rate control drugs, as well as myocardial energy metabolism drugs, must be in keeping with “the 2015 Atrial Fibrillation: Current Understanding and Treatment Recommendations.” The HTDJ and placebo were produced and packed in a single batch (production batch number: HTDJ: 1070649; Placebo: 1070649) by Shanghai Wan Shicheng Pharmaceutical Co., Ltd, which has no conflicts of interest relevant to this study. The test results of drug quality were consistent with the Chinese Medicine Standards of the State Food and Drug Administration. The placebo is composed of 10% crude HTDJ and 90% starch, which have the same appearance and scent as the active treatment drugs. Participants will take one bag twice a day for 4 weeks, while avoiding oral administration of other Traditional Chinese Medicine for efficacy evaluation. Then, do not accept Traditional Chinese Medicine, only western medicine treatment, followed up for 8 weeks, another clinical evaluation.

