### Outcomes

#### Primary outcome

Frequency of atrial fibrillation attacks (from baseline to weeks 4, 8, and 12)
° Significant effects: The frequency of attacks decreased by more than 70%.° Effective: The frequency of attacks decreased between 30% and 70%.° Invalid: The frequency of attacks decreased by less than 30%.° Deterioration: Increased attack frequency.

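### E/A has no value for a participant in AF at the echo, so a between-group test of it loses data and is open to bias if rhythm at follow-up differs between arms

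*Protocol article*

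**What the plan says.** All references are to the protocol article.

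- **Secondary outcomes** heads the cardiac ultrasound item "Echocardiography (from baseline to weeks 4 and 12"). Among its six measures are the "ratio of left ventricular early diastolic fast filling peak to late diastolic filling peak (E/a") and the "ratio of early diastolic velocity of mitral valve to early diastolic annular velocity (E/e").
- **Diagnostic criteria** describe the ECG in AF: the P wave is lost and the f "wave replaces it, the frequency is about 350–600 times".
- **Inclusion criteria** admit participants by attack count: "atrial fibrillation, seizure frequency ≥2 times a month (at least one ECG diagnosis"). No rhythm is required at enrolment or at visits, and the exclusion criteria do not expressly rule out persistent AF.
- **Primary outcome** is "Frequency of atrial fibrillation attacks (from baseline to weeks 4, 8, and 12"), so time spent in AF is what the treatment is meant to reduce.
- **Interventions** allow background drugs that can also change rhythm: "Western medicine includes cardioversion drugs and heart rate control drugs".
- **Statistical analysis** assigns a t test or a non-parametric test to measurement data, with no separate rule for E/A.
- **Criteria for discontinuing or modifying allocated interventions** carries the last main efficacy result forward, but only for discontinued cases.
- **Table 3** schedules ECG and Holter at every visit that has an echocardiogram.

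**The concern.** The late filling peak comes from organised atrial contraction. AF, as the article defines it, is the absence of organised atrial activation, so E/A does not exist in the very state that defines the disease under study. This differs from an ordinary missing value: no observation was lost that could be imputed or carried forward.

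The participants who contribute an E/A at week 4 or 12 are those in sinus rhythm at that moment. Rhythm at follow-up comes after randomisation and is the target of the treatment. If the arms differ in it, the test compares two differently selected subsets, and a difference in E/A could appear, or be hidden, without any effect of treatment on diastolic filling.

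**Working it through.** The article gives no figure for E/A, for rhythm at the echo or for the number analysable, so there is no stated result to reproduce. The logic comes from its own definitions. The size can only be illustrated under assumptions.

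**Inputs from the article.** 30 per group before allowance for loss; 76 in total at 1:1, hence 76/2 = 38 per arm (Sample size; Randomization).

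**Assumed inputs.** Share in AF at each echo, q, from 5% to 30%. For the bias illustration, several pairs of sinus-rhythm shares, and a correlation ρ of 0.3 to 0.5 between E/A and the tendency to be in AF.

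**1. Data lost when the arms have equal shares.** A change from baseline needs sinus rhythm at both scans. If rhythm is independent between visits, usable pairs per arm = 30 × (1 − q)²:

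- q = 0.05: 30 × 0.95² = 27.1
- q = 0.30: 30 × 0.70² = 14.7

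If instead the same participants are in AF at both scans, pairs = 30 × (1 − q), that is 28.5 and 21. Because q is the same in both arms, these figures show lost precision and nothing about bias.

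**2. Which part of the selection can bias.** Needing sinus rhythm at baseline selects on a pre-randomisation feature. It narrows the population but leaves the arms comparable. Only selection on rhythm at week 4 or 12 can separate the arms.

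**3. Illustration of bias when shares differ.** Suppose treatment has no effect on E/A itself. A standard normal tendency towards AF has correlation ρ with E/A (in SD units), and a participant is in sinus rhythm when that tendency lies below the cut-off z(s) that gives sinus-rhythm share s. Then

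- spurious difference = ρ × [φ(z(s_C))/s_C − φ(z(s_T))/s_T]
- SE = √(1/n_T + 1/n_C), with n = 38 × s
- false-positive rate = Φ(d/SE − 1.96) + Φ(−d/SE − 1.96), two-sided 5% level

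Example, 80% vs 60% with ρ = 0.5: d = 0.5 × (0.644 − 0.350) = 0.147. With n = 30.4 and 22.8, SE = 0.277. The rate is Φ(−1.43) + Φ(−2.49) = 0.0764 + 0.0064, about 8%.

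| Sinus rhythm at follow-up, treatment vs control (assumed) | Spurious difference, ρ = 0.3 to 0.5 | False-positive rate |
|---|---|---|
| 70% vs 70% | 0 | 5% |
| 95% vs 90% | 0.03 to 0.04 SD | 5.1% to 5.4% |
| 80% vs 60% | 0.09 to 0.15 SD | 6% to 8% |
| 90% vs 50% | 0.18 to 0.30 SD | 10% to 18% |

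The direction depends on how E/A relates to the tendency to be in AF, which the article does not give.

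**The case against.** The strongest reply is that this is silence rather than error. The article is a condensed account, and scan conditions and the handling of unobtainable values usually sit in an echo manual or an analysis plan. It nowhere says that the E/A test will be confined to sinus rhythm, nor that E/A is unmeasurable in AF. Entry by countable attacks also implies an intermittent rhythm, so many participants may be in sinus rhythm at a booked visit.

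Part of this stands. The point about entry by attack count is sound, and it means the loss may be small. The limit to sinus rhythm is indeed an inference, but it follows from the article's definition of the ratio, its definition of AF and basic physiology. Leaving the matter to a later document does not dispose of it, because no analysis rule can recover a value that does not exist, and the choice of outcome is fixed here. The carry-forward rule does not help either: a participant who attends in AF has not discontinued.

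A reader might go further and infer that the E/A comparison is bound to be biased, or that the fall from about 27 to 15 pairs measures that bias. The documents support neither. They give no rhythm shares by arm, the pairs calculation assumes equal arms, and the first two rows of the table show no bias or a negligible one. Nor does the article say that E/e is valid in either rhythm. What can be said from its definition is that it uses early-diastolic velocities only and does not need the atrial peak.

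**Conclusion.** The point holds in a limited form. E/A is fixed as an outcome at weeks 4 and 12 although it has no value for a participant in AF at the scan, so any between-group test rests on those in sinus rhythm at that visit. Loss of data is certain if anyone is in AF at an echo. Bias arises only if rhythm at follow-up differs between arms; that is possible under the trial's own hypothesis, but its size is unknown. Every figure for loss and bias above depends on assumed rhythm shares, and the bias figures also on an assumed correlation.

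One of six measures within one secondary outcome is affected. The primary outcome, the sample size and the safety assessment are untouched. This is a cheap improvement, not a threat to the trial's main conclusion.

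**What to change.** Add a sentence to the echocardiography item under Secondary outcomes, to this effect: rhythm at each echocardiogram is recorded from the ECG of the same visit; E/A is summarised descriptively, by arm, for participants in sinus rhythm, together with the number in AF in each arm; the between-group comparison of diastolic function uses E/e.

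No new test is needed, since Table 3 already schedules ECG alongside the echocardiogram and E/e is already on the outcome list. The cost is that E/A no longer has a p-value. Showing the number in AF by arm also lets readers judge for themselves how far selection could have affected the E/A summary.

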**Method:**

This study adopts a randomized double-blind, single-simulated, placebo-controlled research method. Participants were randomly assigned in a 1:1 ratio through a centrally controlled, computer-generated, simple randomization schedule. Participants would take the medicine for 1 month, and the curative effect would be evaluated. Subsequently, the participants would not take TCM and only receive western medicine treatment. They would be followed up for another 8 weeks, and a clinical evaluation would be conducted. The secondary outcomes include echocardiography, Hamilton Anxiety Scale, Hamilton Depression Scale, rate of increase and decrease of anti-arrhythmia western medicine, the MOS 36-item short-form health survey, N-terminal-pro hormone B-type natriuretic peptide level, and integral TCM syndrome score. Adverse events will be monitored throughout the trial. Cases are from outpatient and inpatient with atrial fibrillation in the Cardiology Department of Longhua Hospital. Evaluations will be conducted at baseline and at weeks 4 and 12 after randomization.

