### Safety monitoring

Routine blood test, liver and kidney function test, electrolytes test, and urine test (from baseline to weeks 4) are the basic indicators that reflect the general situation and basic safety evaluation.

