### Research process record points

The subject content and data at each time point, according to the patient’s hospitalization period, will be recorded as shown in Table 1. Specifically, the screening period (−3~0 days) will be 0 to 3 days before recruitment. The 4-week treatment period was planned in two cycles of 2 weeks, with a return visit between cycles to check for AEs and monitor compliance. All interventions will be stopped after 4 weeks. Follow-up will be conducted on weeks 4 and 12. The detailed information is shown in Table 3.

**Table 3 Tab3:** Research flowchart

Activity	Phase(time points)	Screening stage	baseline period	intervention	Follow-up	
		−3d~0d	0d	4w	8w	12w
**Enrolment**	Sign informed consent	✔				
	Inclusion and exclusion criteria	✔				
	Demographic data	✔				
	Medical history and treatment history	✔				
	Basic data collection	✔				
**Outcome assessment**	Frequency of atrial fibrillation		✔	✔	✔	✔
	ECG and Holter		✔	✔	✔	✔
	Ultrasonic cardiogram		✔	✔	✔	✔
	TCM clinical syndrome integral		✔	✔	✔	✔
	Rate of increase and decrease of anti-arrhythmia western medicine		✔	✔	✔	✔
	NT-proBNP		✔			✔
	Hamilton Anxiety Scale		✔	✔	✔	✔
	Hamilton Depression Scale		✔	✔	✔	✔
	SF-36		✔	✔	✔	✔
	PVO		✔	✔	✔	✔
	Anaerobic threshold		✔	✔	✔	✔
**Safety assessment**	Physical examination		✔	✔	✔	✔
	Blood routine examination		✔	✔		
	Urine routine and urinary sediment		✔	✔		
	Liver function		✔	✔		
	Renal function		✔	✔		
	Blood lipid		✔	✔		
	GLU		✔	✔		
	INR		✔	✔		
	CHA2DS2-VAS		✔	✔		
	HAS-BCED		✔	✔		
**Other information**	Randomization	✔				
	Hemorrhage		✔	✔	✔	✔
	Readmission		✔	✔	✔	✔

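### Table 3 schedules no NT-proBNP sample at week 4, although the outcome definition requires one at the end of treatment

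*Protocol article*

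**What the plan says.** All places are in the protocol article.

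- **Secondary outcomes** gives the timing as "NT-proBNP (from baseline to weeks 4 and12" and the purpose as "Changes in the levels of NT-proBNP in each group will be measured before and after treatment".
- **Interventions** and **Research process record points** put the end of study treatment at week 4. Eight weeks on western medicine alone follow.
- **Table 3** (under Research process record points) has columns for screening, day 0, and weeks 4, 8 and 12. Its NT-proBNP row is ticked at day 0 and week 12 only.
- **Primary outcome** reads "Frequency of atrial fibrillation attacks (from baseline to weeks 4, 8, and 12". The Hamilton anxiety and depression scales, SF-36 and the change in antiarrhythmic drugs have the same weeks under Secondary outcomes. Table 3 ticks all five at week 8.
- Two summary sentences leave week 8 out. The abstract says "Evaluations will be conducted at baseline and at weeks 4 and 12 after randomization", and the text above Table 3 says "Follow-up will be conducted on weeks 4 and 12".
- **Safety monitoring** names, after blood, liver and kidney tests, "electrolytes test, and urine test (from baseline to weeks 4".
- The text above Table 3 also plans two 2-week cycles "with a return visit between cycles to check for AEs and monitor compliance".

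**The concern.** An outcome can be analysed at a given time only if it is measured then. The definition of NT-proBNP asks for an end-of-treatment value, and the schedule table does not provide one. The week 4 value is the one that speaks to the effect of HTDJ while it is being taken. The week 12 value, after 8 weeks without study drug, answers a different question: whether any effect persists. If only week 12 is collected, a null result could mean either no effect on treatment or an effect that had worn off, and the data could not separate the two.

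The remaining mismatches raise a smaller worry. Readers and staff meet more than one list of visits and cannot tell from the article which one governs.

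**Working it through.** No formula applies. The check sets the times in the text beside the ticks in Table 3.

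| Item | Times in the defining text | Times in Table 3 | Result |
|---|---|---|---|
| NT-proBNP | 0, 4, 12 | 0, 12 | **Week 4 absent from the table** |
| AF attack frequency (primary) | 0, 4, 8, 12 | 0, 4, 8, 12 | Agree |
| Anxiety scale, depression scale, SF-36, antiarrhythmic drug change | 0, 4, 8, 12 | 0, 4, 8, 12 | Agree |
| Echocardiography, TCM score | 0, 4, 12 | 0, 4, 8, 12 | Week 8 extra in the table |
| Electrolytes | 0, 4 | no row | Absent from the table |
| Return visit between the 2-week cycles | about week 2 | no column | Absent from the table |

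1. **NT-proBNP.** The definition has three times and the row has two ticks. Shifting the columns cannot make two ticks cover three times, so a misaligned table does not explain the gap. The ticks fall in the first and last of the four measurement columns, with weeks 4 and 8 blank between them.
2. **Consequence if the table is followed.** Week 4 samples planned: 0 of 76. The only post-baseline sample is at week 12, which is 12 − 4 = 8 weeks after treatment ends.
3. **Feasibility of the week 4 sample.** Table 3 ticks routine blood, liver function, renal function, lipids, glucose and INR at week 4, so blood is already being drawn at that visit.
4. **Week 8.** The primary outcome definition, the secondary outcome definitions and Table 3 agree on week 8 for the primary outcome and four secondary measures. Only the two summary sentences omit it. The one above Table 3 is followed at once by a pointer to that table for detail.
5. **Electrolytes and the mid-treatment visit.** These are mismatches with the safety and schedule text, not with an outcome definition. Safety monitoring lists electrolytes separately from kidney function, so the renal row does not plainly include them.
6. **Echocardiography and TCM score.** The table asks for more than the definitions need, so no defined data are lost.

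**The case against.** **Week 12 is also after treatment.** The before-and-after wording could loosely be met by a week 12 sample. That does not settle the matter, because the same entry names week 4 explicitly.

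**The working instruments are not shown.** This is one hospital, with data going into a CRF and REDCap. Those may already carry a week 4 NT-proBNP field. This stands: the loss is conditional on staff following Table 3, and the article does not show which version is in use.

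**A stronger reading: week 8 primary data will be missing.** A reader might infer this from the two summary sentences. The documents do not support it. Week 8 would be lost only if staff set aside the primary outcome definition, the secondary outcome definitions and Table 3 together. Nor can one argument assume both that staff follow the table (losing NT-proBNP at week 4) and that they ignore it (losing week 8). Neither sentence says that the weeks it lists are the only ones. What remains is loose wording.

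**The other items are minor.** This too is largely right. The electrolytes test and the return visit are stated outright in the text, and a missing row or column does not cancel them. Electrolytes may be run with the renal panel. Table 3 has no general adverse-event or compliance row at any visit, so the missing column may only reflect what the table leaves out.

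**Correction comes late.** Recruitment began on April 15, 2020 and was to finish on January 1, 2022; the article appeared on October 11, 2021. A sample not taken at week 4 cannot be recovered by editing a table. This stands, and the fix allows for it.

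**Conclusion.** The contradiction on NT-proBNP is real and lies wholly within the article: three times are defined and two are scheduled, and the one left out is the end of treatment. If Table 3 governs, week 4 NT-proBNP is unavailable for every participant and the outcome can be compared only 8 weeks after study drug stops. If the outcome section governs, nothing is lost and the table is simply wrong. The article does not say which takes precedence.

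The effect is limited to one secondary outcome. It does not invalidate the trial, and it does not put the primary outcome's week 8 data at material risk. The summary sentences, electrolytes, the return visit, and the extra week 8 ticks for echocardiography and TCM score are genuine mismatches that call for reconciliation, nothing more.

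**What to change.** 1. Tick NT-proBNP at week 4 in Table 3, and confirm that the CRF and REDCap have the matching field. The cost is one added assay on blood drawn at an existing visit, which the outcome section already promises.
2. For participants already past week 4 without a sample, report the week 4 value as not collected and give the number per group. Do not let the week 12 value stand in for it.
3. Change the two summary sentences, in the abstract and above Table 3, to weeks 4, 8 and 12.
4. Reconcile Table 3 with the text on the electrolytes test and the return visit between cycles, so that each appears the same way in both places.
5. Give echocardiography and the TCM score one set of visits in both places. If week 8 is kept in the table, state whether it belongs to the outcome definition.

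Items 3 to 5 are wording and table edits; any change to what is collected for item 4 or 5 depends on how the sponsor resolves them.
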